### Inclusion and exclusion criteria

#### Inclusion criteria

Children aged 8–15 years of age (inclusive) for females and 9–17 years of age (inclusive) for males with reversed I-GHD (peak GH ≥ 6.7 μg/L using arginine or insulin tolerance test and a serum IGF-1 within normal reference range for sex and age), normal brain MRI (including small anterior pituitary) and in established puberty (Tanner stages B2/3 in girls and 6–12 ml testes* in boys (as measured by orchidometer**)The initial diagnosis of I-GHD will have been made by either two GH stimulation tests (peak GH < 6.7 μg/L) or one stimulation test (peak GH < 6.7 μg/L) with IGF-1 below normal range for sex and age (< -2SDS) irrespective of sex-hormone priming for GH stimulation testsChildren will have discontinued GH treatment for a minimum of 6 weeks prior to re-testingAbility to tolerate the administration of GH therapyAbility to comply with trial schedule and follow-up

Written informed consent obtained from the patient’s parent/guardian and written assent obtained from patient (where age appropriate). In the UK, patients aged 16 years or older will provide their own written informed consent.

*In the event of discrepancy between the size of an individual’s testicles, the larger testicle should be used.

**In the event that the size of a patient’s testicle falls between the measuring beads of the orchidometer and it is not clear which bead the testicle is most similar to, the larger bead should be used.

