#### Planned interventions

Participants in the control arm (GH +) will resume receiving their GH treatment at a dosing level determined by their clinical care team (following the minimum 6-week discontinuation period required prior to randomisation). Participants in the experimental arm (GH −) will not resume GH treatment. Both arms will be followed up at 6 monthly intervals until near FH or the 36-month follow-up (whichever is soonest).

All currently available GH treatment preparations with the active ingredient Somatropin are allowed, as detailed in the British National Formulary for Children (BNFc) in the UK and Kindermedika in Austria (https://kindermedika.at/monographie/10222/somatropin).

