#### Sample size and power calculation

Determination of non-inferiority margin was carefully considered, following extensive consultation. A questionnaire was sent to all investigators, British Society for Paediatric Endocrinology and Diabetes clinical study group members, and a patient support group representative (*n* = 34), giving several options for ‘acceptable deficit’ in various FH outcomes. These FH outcome options for comparison between the GH + and GH − groups were (1) the percentage of children reaching normal adult height (0 ± 2SD), (2) the percentage of children reaching mid-parental TH (0 ± 2SD) and (3) the near FH (in SDS/cm). Near-FH standard deviation score (near FH-SDS) was selected as the primary outcome.

Whilst the percentage of children reaching mid-parental TH [26] was the most popular outcome amongst respondents, data were not available to inform a sample size calculation. However, all the above options to express FH will be analysed in this trial as secondary outcomes. Other secondary outcomes are HRQoL, lipid profile, cost-effectiveness, and the bone health index (assessing effect of GH + /GH − on bone accrual and bone age using BoneXpert software).

For the primary outcome measure of near FH-SDS with a non-inferiority design comparing means and assuming equal variance, a non-inferiority margin of 0.55 near FH-SDS, a one-sided test with alpha = 0.025 and 90% power, a group size of 57 (total *n* = 114) would be needed (calculated using the SSI procedure in Stata 13). This calculation was based on a near FH-SDS (SD) of − 1.6 (0.9) using data from a population-based registry for patients with idiopathic GHD treated with GH and completing the scheduled treatment [27]. The non-inferiority margin is based on clinical opinion. Additional observational studies gave consistent results. Using the LMS growth software, a 0.55 height SDS score (using British 1990 Growth Charts [28]) approximates to 3.8 cm for boys and 3.3 cm for girls at age 23. With 17% allowance for withdrawal and loss to follow-up, a total sample size of 138 is required.

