### Missing data and sensitivity analyses

Every attempt will be made to collect full follow-up data on all trial participants; it is thus anticipated that missing data will be minimal. Participants with missing primary outcome data will not be included in the primary analysis in the first instance. This presents a risk of bias, and sensitivity analyses will be undertaken to assess the effect of any missing data. In brief, this will include a multiple imputation approach, using important variables to predict the near FH SDS and a last observation carried forward (LOCF) approach, which assumes no change from the previous assessment.

A further sensitivity analysis will be conducted to assess the impact of participants who have not reached near FH by the end of the study. For the primary analysis, all participants will be included and for any participants who have not reached near FH, their height recorded at the end of study follow-up visit will be used. Although we anticipate this to be a rare event, we will conduct a sensitivity analysis (for the primary outcome only) which excludes any participants who have not reached near FH by the end of the study. Full details are included in the SAP.

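### LOCF can understate a height deficit that builds up through puberty, so it is a weak robustness check for missing near final height in this non-inferiority trial

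*Protocol article*

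**What the plan says.** The section on missing data and sensitivity analyses makes the primary analysis complete-case: "Participants with missing primary outcome data will not be included in the primary analysis in the first instance". It recognises the consequence: "This presents a risk of bias, and sensitivity analyses will be undertaken to assess the effect of any missing data". Two checks follow. For the first, "this will include a multiple imputation approach, using important variables to predict the near FH SDS". The second is "a last observation carried forward (LOCF) approach, which assumes no change from the previous assessment". The section refers to the SAP for full details, and the SAP is not shown.

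Three other places bear on the point:

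- **Inclusion criteria and Planned interventions.** Children enter at Tanner B2/3 or with 6–12 ml testes. They are seen every 6 months until near final height or month 36.
- **Primary outcome measure.** Non-inferiority requires the lower 95% confidence limit to lie above −0.55 in both the ITT and the per-protocol analysis.
- **Statistical analysis.** ITT is paired with per-protocol because ITT on its own could favour non-inferiority. No similar caution is attached to LOCF.

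**The concern.** The endpoint is meaningful only because these children still have growth ahead of them at randomisation. If stopping growth hormone costs height, the loss appears gradually over the following visits. An SDS carried forward from an early visit was recorded before much of that loss could occur. Using it as the final value sets the treatment effect after dropout to zero.

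In a superiority trial, shrinking the difference between arms is usually the cautious direction. In a non-inferiority trial it is the favourable one. A check meant to expose bias from missing outcomes could therefore agree with the primary result because of how it is built, and a reader could take that agreement as evidence of robustness.

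**Working it through.** **Inputs from the protocol article (Sample size and power calculation):** margin 0.55 SDS, one-sided alpha 0.025, power 90%, SD 0.9, 57 per arm (114 in total), 17% allowance for loss, 138 randomised. Allocation is 1:1, so 69 per arm.

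**Reproducing the plan's figure.** n per arm = 2 × [0.9 × (1.960 + 1.282) / 0.55]² = 56.3, rounded up to 57; total 114. Then 114 / 0.83 = 137.3, rounded up to 138. Both agree with the article.

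**Assumptions, not given in the documents:**

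- The true deficit at near final height is D = 0.55, exactly at the margin.
- A share d is missing in each arm, for reasons unrelated to growth.
- A share f of the deficit is already visible at the last recorded visit.
- SDS is the quantity carried, and carried values have the same SD of 0.9.

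**Formulas.**

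- Expected LOCF difference = D × [(1 − d) + d × f].
- SE = 0.9 × √(2/69) = 0.153.
- Chance that the LOCF analysis, taken alone, meets the margin = Φ[(0.55 − expected difference) / SE − 1.96].

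**Worked case, d = 0.17 and f = 0.** The difference is 0.55 × 0.83 = 0.4565. The shift is 0.0935, and 0.0935 / 0.153 = 0.61. Φ(0.61 − 1.96) = 8.9%.

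| Missing (d) | Deficit visible (f) | LOCF difference | Meets margin |
|---|---|---|---|
| 17% | 0 | 0.457 | 8.9% |
| 17% | 0.5 | 0.503 | 4.9% |
| 17% | 0.75 | 0.527 | 3.5% |
| 17% | 1 | 0.550 | 2.5% |
| 10% | 0 | 0.495 | 5.5% |
| 10% | 0.5 | 0.5225 | 3.7% |
| 5% | 0 | 0.5225 | 3.7% |

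The last two rows are the same case arithmetically: both shift the difference by 0.0275, giving 0.0375.

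**Comparison with complete cases.** Under the same random loss the complete-case difference is 0.55 in expectation, and that analysis meets the margin 2.5% of the time. With d = 0.17 and f = 0, the true deficit would have to reach 0.55 / 0.83 = 0.66 before the expected LOCF difference equalled the margin.

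**Effect of baseline adjustment.** The primary model adjusts for baseline height SDS, which reduces the residual SD. With an assumed baseline correlation of 0.5, the SD becomes 0.9 × √(1 − 0.25) = 0.78. The two leading figures at 17% missing then become 10.5% (f = 0) and 5.4% (f = 0.5).

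**The case against.** Four objections have force.

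**LOCF does not decide the trial.** A reader might infer that the false-positive rate of the trial rises to 8.9%. The documents do not support that. The section on the primary outcome measure rests the conclusion on the ITT and per-protocol analyses, and LOCF is neither. The 8.9% belongs to the LOCF analysis alone. It is also a corner case: it needs the full 17% loss and no deficit visible at any last visit, although visits are 6-monthly.

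**The direction is not fixed.** A reader might infer that LOCF always favours non-inferiority. It does not.

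- With no true difference and equal loss it is neutral.
- If poorly growing children who stopped treatment leave selectively, LOCF keeps part of their shortfall while complete-case analysis drops it. For illustration, assume 17% missing, a deficit of 0.40 in completers and 1.0 in dropouts, with half of the latter visible. Complete-case gives 0.40, LOCF gives 0.83 × 0.40 + 0.17 × 0.50 = 0.417, and the full deficit is 0.83 × 0.40 + 0.17 × 1.0 = 0.502. LOCF moves the right way but recovers little.
- The article does not say whether SDS or centimetres are carried. If centimetres were scored on an adult reference, with carried values assumed 1 SDS short, no other deficit visible in them, and loss of 25% after stopping against 9% after continuing, the difference would be 0.55 × 0.75 + 0.25 − 0.09 = 0.57, beyond the margin.

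**Constant SDS is not constant height.** A growing child can hold the same SDS, and a child lost shortly before near final height changes little. It would be wrong to say that the assumption fails for every participant.

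**Expected and allowed loss can differ.** The article says "it is thus anticipated that missing data will be minimal" and also plans a 17% "allowance for withdrawal and loss to follow-up, a total sample size of 138 is required". A reader might see a contradiction. A cautious allowance and a hopeful expectation can both stand, and the point does not depend on it.

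**Conclusion.** The point holds in a limited form. LOCF is a stated method, and its stated assumption fits poorly with children enrolled in mid-puberty and followed for up to 36 months. If loss is unrelated to growth and a true deficit exists, LOCF understates that deficit and is less cautious than the analysis it is supposed to test. At 17% loss and a deficit at the margin, the understatement ranges from none, if the deficit was fully visible at the last visit, to 0.09 SDS, if none of it was. At 5% loss it is at most 0.03 SDS. These sizes rest on assumed values of the visible share, which the documents do not supply.

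The consequence is a robustness check that may mislead. Multiple imputation is planned beside it, which limits the damage. It cannot be inferred that the plan lacks any analysis under less favourable missing-data assumptions, because the article gives its methods only in brief and the SAP is not shown. Nor does this point require the complete-case primary analysis to be replaced.

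**What to change.** Remove LOCF from the sensitivity analyses. If it is kept, label it as non-conservative for a non-inferiority conclusion and state whether SDS or centimetres are carried.

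Build the planned multiple imputation on the 6-monthly heights already collected. Add a delta-adjusted tipping-point analysis that shifts the imputed near final height SDS in the discontinuation arm down in steps from 0 to at least −0.55, and report the shift at which non-inferiority is lost. The complete-case primary analysis can stay as it is.

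The cost is revised wording in the protocol and SAP and a little more analysis work, with no new data collection. The downside for the sponsor is that the resulting robustness statement may be less favourable.

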**Fig. 2 Fig2:**
[figure not shown]
GHD Reversal Trial schedule of assessments. Three asterisks (***) indicate the following: patients will be followed up until ‘Near FH (growth rate < 2 cm/year and bone age of 14 and 16 for males and females respectively). Given the usual duration of pubertal growth until FH is reached, 3 years follow-up has been allowed for; however, if patients do not reach near FH by 3 years, this may be longer

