#### Study procedures

Routine retesting in established puberty is routine clinical practice in all trial sites. Children with GHD persistence at retesting will restart GH; those with GHD reversal will be offered study participation. Following consent, participants will be randomised to GH + (25–35 µg/kg/day) and GH − groups and followed in routine endocrine clinics until ‘Near FH’ (growth rate < 2 cm/year) is reached. In the GH − group, any unexpected decrease in IGF-1 concentrations below − 2 SD (lower limit of normal) at 6 months would trigger a repeat GH stimulation test and recommencement of GH if deficient.

The baseline visit for all patients will include confirmation of inclusion and exclusion criteria, informed consent/assent, randomisation and allocation of trial number, prescription of growth hormone (if randomised to continue treatment), a record of the preparation and dose prescribed, a record of concomitant medication and relevant medical history. Height, weight and Tanner stage will also be measured at baseline. All patients will have 6-monthly visits to measure height, weight, Tanner stage, serum IGF-1 (at 6 months and annually thereafter) as well as checking compliance with GH therapy and any concomitant medication and adverse event reporting. HRQoL will be measured using the CHU9D questionnaire at baseline and at each 6-monthly visit. A left hand X-ray will be conducted at enrolment and near FH, for central analysis using the BoneXpert software. Fasting lipids will be measured at baseline and near FH.

At near FH, all subjects will have a GH stimulation test to reconfirm GH status. Given the usual duration of pubertal growth until near FH is achieved, we have allowed for 3 years follow-up.

The information captured at the randomisation and subsequent visits are shown in Fig. 2.

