## Discussion and potential impact

Five previous studies have demonstrated reversal of GHD (mean 49%; range 19–95%) with earlier re-testing, before or during puberty [4–6, 15, 16]. One study found that children with GHD reversal confirmed during puberty reach their target height (TH) without further GH therapy [6]. Another study showed that children stopping GH 1.6 years before attaining FH achieve a similar FH to those who continue taking GH until they reach their FH [30]. A GH stimulation test is usually performed when FH is attained to assess any requirement for adult GH therapy, and it is at this point that many patients are found to be no longer GH deficient. This study will test whether the near FH of those stopping GH treatment is not inferior to the near FH of those continuing and is thus the first study to our knowledge that is a randomised controlled trial. If this study shows that a significant proportion of children with I-GHD generate enough GH naturally in early puberty to reach a near FH within the target range, this new care pathway could rapidly improve practice; it would relieve patients from the diagnostic uncertainty of GHD persistence and may allow patients to stop GH therapy approximately 3 years earlier, and still reach a normal near FH without the burden of daily injections, and at considerably reduced health care cost. Based on published data, we can assume that on a 50% reversal rate, the potential cost savings for the NHS would be in the range of £1.8–4.6 million (€2.05–5.24 million)/year in drug costs alone [2]. It is important to note that GH treatment is not without its problems. Previous studies have suggested rare side-effects including benign intracranial hypertension, diabetes and slipped femoral capital epiphysis in association with GH treatment [30]. However, more recent data have suggested significant risks potentially associated with GH treatment. In those patients with normal GH secretion who were treated with high doses of GH, a higher incidence of bone tumours was reported [32]. Additionally, further data from the SaGHe study have revealed an increased incidence of cerebrovascular events in patients who previously received GH treatment [33]. However, more recently, detailed registry reviews indicated no increased risk of strokes or cancer, once risk factors had been accounted for [34]. Nonetheless, some controversy remains around safety of GH therapy, and it would be important to ensure that GH should only be considered in those patients who would benefit from its use, with a view to minimising any adverse effects.

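### Children still growing at the end of the study enter the primary analysis with an unfinished height, and the plan calls this rare without giving a basis

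*Protocol article*

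**What the plan says.** All references are to the protocol article; the SAP is not at hand.

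- **Missing data and sensitivity analyses.** All participants enter the primary analysis, and "for any participants who have not reached near FH, their height recorded at the end of study follow-up visit will be used". The next sentence begins "Although we anticipate this to be a rare event" and commits to a sensitivity analysis, on the primary outcome only, that leaves these children out. Further detail is deferred to the SAP.
- **Planned interventions.** The limit on follow-up: "Both arms will be followed up at 6 monthly intervals until near FH or the 36-month follow-up (whichever is soonest". Planned final analyses times the primary analysis on the same terms.
- **Study procedures.** The basis for the limit: "Given the usual duration of pubertal growth until near FH is achieved, we have allowed for 3 years follow-up".
- **Legend to Fig. 2.** A different rule: "if patients do not reach near FH by 3 years, this may be longer".
- **Discussion and potential impact.** Early re-testing "may allow patients to stop GH therapy approximately 3 years earlier".
- **Primary outcome measure.** Non-inferiority needs the lower 95% confidence limit above −0.55 SDS in both the ITT and the per-protocol analysis.

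**The concern.** By the definition in Planned final analyses, a child not at near FH is still growing at 2 cm/year or more, or has not reached the required bone age. That child's last height is not near FH: it omits the growth to come and any treatment difference still to appear. Using it amounts to carrying the last observation forward, in a child for whom no further change is known to be a poor assumption. For missing data the plan confines that method to a sensitivity analysis.

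This would matter little if such children were few. The article says they will be, but offers no figure, and its stated reason for 3 years is that this is the usual duration. A limit placed near a typical duration, with no stated reserve, would be passed by more than a few.

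At stake is the meaning of the primary estimate. If GH+ children grow for longer, their heights are understated and false non-inferiority becomes more likely. If GH− children grow for longer, a deficit is manufactured and power is lost. Requiring the per-protocol analysis as well is no protection if it uses the same substitution.

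**Working it through.** **1. The plan's own figure.** From Sample size and power calculation: margin 0.55, SD 0.9, one-sided alpha 0.025, power 90%.

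n per arm = 2(1.960 + 1.282)² × 0.9² / 0.55² = 56.3, so 57, or 114 in total; 114 / 0.83 = 137.3, so 138. The stated size reproduces. SE = 0.9 × √(2/57) = 0.1686, and power = Φ(0.55/0.1686 − 1.960) = 90.4%.

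**2. Share unfinished at 36 months.** The document gives no distribution. Assume time T from randomisation to near FH is normal; share = 1 − Φ((3 − mean)/SD).

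| Mean (years) | SD 0.5 | SD 0.75 | SD 1.0 |
|---|---|---|---|
| 2.0 | 2% | 9% | 16% |
| 2.5 | 16% | 25% | 31% |
| 3.0 | 50% | 50% | 50% |

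For a share of 5% or less, the mean must be at most 3 − 1.645 × SD: 2.18, 2.01, 1.77 or 1.36 years for SD 0.5, 0.6, 0.75 or 1.0.

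**3. Bias if tempo differs by arm.** Assumptions, none from the document except where noted:
- Growth is 2 cm/year at near FH and 2 cm/year faster for each year before it, so a child r years short has 2r + r² cm left.
- 1 SDS is 6.5 cm, against an adult reference. The article equates 0.55 SDS with 3.8 cm (boys) and 3.3 cm (girls), that is 6.9 and 6.0 cm per SDS.
- The arms differ in mean T by 0.25–0.5 year, split equally about the overall mean. The SE stays at 0.1686.

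With d = (mean − 3)/SD, E[r] = SD[φ(d) + dΦ(d)] and E[r²] = SD²[(1 + d²)Φ(d) + dφ(d)]. The bias B is the between-arm difference in (2E[r] + E[r²])/6.5.

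Example: mean 3.0, SD 0.75, GH+ half a year longer (arm means 3.25 and 2.75). E[r] = 0.4407 and 0.1907; E[r²] = 0.4649 and 0.1601. B = (2 × 0.2500 + 0.3048)/6.5 = 0.124 SDS. At a true deficit of 0.55 the chance of passing is Φ(0.124/0.1686 − 1.960) = 11%. With the tempo difference reversed and no true deficit, power is Φ((0.55 − 0.124)/0.1686 − 1.960) = about 72%.

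| Mean, with SD 0.5–0.75 | B (SDS) | One-sided error, GH+ longer | Power, GH− longer |
|---|---|---|---|
| 2.5 | 0.016–0.058 | 3–5% | 89–83% |
| 3.0 | 0.054–0.124 | 5–11% | 84–72% |

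At SD 1.0 with a 0.5-year difference, B is 0.079 (mean 2.5) or 0.139 (mean 3.0), and the error is 7% or 13%.

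**4. Bias if a deficit is still building, with equal tempo.** If a share p is unfinished and shows a fraction f of a true 0.55 deficit, the observed deficit is 0.55[1 − p(1 − f)]. For p = 16%, 31% and 50%, the chance of passing is 3.4%, 4.4% and 6.0% at f = 0.75. It is 1.8%, 1.4% and 0.9% at f = 1.25, which represents GH− children catching up later.

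**5. The excluding analysis.** The 17% allowance is for withdrawal and loss, so exclusions come off the 57. With 57(1 − p) per arm, power is 85%, 77% and 64% at p = 16%, 31% and 50%.

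**6. Effect of following to a common close.** Recruitment of 42 months (Trial status) plus 36 is 78 of the 90 trial months (Study design). With uniform recruitment, each child has 3 years plus 0 to 3.5 more, so the share unfinished is about E[r]/3.5. Mean 2.5: 0.042/3.5 to 0.198/3.5, or 1–6% (SD 0.5–1.0). Mean 3.0: 0.199/3.5 to 0.399/3.5, or 6–11%.

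**The case against.** A reader might infer that the plan's own 3-year figure shows unfinished children to be common. The document does not go that far. An allowance of 3 years can be read as one that covers the usual duration rather than sits at its middle. The Discussion's saving of about 3 years is measured against treatment to final height, which comes after near FH, and its clock starts when GH stops, at least 6 weeks before re-testing. It is not an estimate of time from randomisation to near FH.

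A reader might also infer that the problem is the same whichever follow-up rule applies. It is not. The Fig. 2 legend allows follow-up beyond 3 years, and step 6 shows the share falling from 16–50% to about 1–11%. On that reading the plan's expectation may be near the mark.

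Nor should one infer a bias towards non-inferiority. The tempo difference is assumed, either sign is possible, and the size depends on whether the WHO SDS is taken at actual age or against an adult standard, which the article does not say.

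Finally, the plan discloses the issue and pre-specifies a check. That deserves credit, but the check is weak. Excluding these children selects on a post-randomisation event that treatment may affect, it loses power, and it does not govern the conclusion.

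What survives is that the primary rule is fixed in the article, its only reassurance is an unsupported word, and two follow-up rules conflict.

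**Conclusion.** The point holds in a limited form. The primary analysis admits a quantity other than near FH for an unstated share of children, and the expectation that this is rare has no support in the document. For under about 5% unfinished at 36 months, the mean time to near FH would have to be about 2 years or less (SD 0.5–0.6). At means of 2.5–3.0 years the share is 16–50%.

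The consequence for the decision is conditional. With a 0.25–0.5 year tempo difference, one-sided error is about 3–11% or power about 72–89%, depending on which arm grows longer, against 2.5% and 90%. All of this rests on a normal time to near FH, an assumed growth curve and an adult SDS reference. The sample size is unaffected. This should be corrected, but it does not undermine the design.

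**What to change.** 1. Reconcile the 36-month limit in Planned interventions with the longer follow-up in the Fig. 2 legend. Reconcile also the near FH bone ages, which are assigned to the opposite sexes in that legend and in Planned final analyses, since they decide who counts as unfinished. For children unfinished at 36 months, use in the primary analysis the height at near FH, or failing that the latest routine clinic height, up to the common closing date. Ethical considerations states that usual care includes monitoring to FH, so such heights should exist.
2. For those still unfinished, pre-specify an analysis that treats near FH as unobserved and imputes it within arm from serial heights, last growth rate, sex, Tanner stage and baseline bone age. Report it beside the raw-height and excluding analyses, and require the non-inferiority conclusion to be interpreted against it. Making it the primary analysis is debatable, because it extrapolates from children who finished sooner.
3. Delete or justify the statement that the event is rare, and report the number unfinished in each arm.

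The cost is wording in the protocol and SAP, some extra routine heights and one more model-based analysis. No further patients are needed, and the 78 months fit within the planned 90.

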#### Randomisation

Following confirmation of patient eligibility, receipt of informed consent and completion of all questions and data items on the randomisation form, the patient will be randomised at the level of the individual in a 1:1 ratio to either continue (GH +) or discontinue (GH −) growth hormone therapy. Randomisation will be provided by a secure online randomisation system at Birmingham Clinical Trials Unit (BCTU). A minimisation algorithm will be used within the online randomisation system to ensure balance in the treatment allocation over the following variables:Tanner stage (B2 (females) or 6– < 9 ml testicular volume of the largest testicle (males) vs B3 (females) or 9–12 ml testicular volume (males).Sex (male vs female).Participating centre.

Following randomisation, a confirmatory e-mail will be sent to the responsible clinician including the child’s trial number and treatment allocation.

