### Planned final analyses

The primary analysis for the trial will occur once all participants have either fulfilled the near FH definition (growth rate of < 2 cm/year and have reached a bone age of 14 years (females) or 16 years (males)), have completed the 36-month assessment or have withdrawn from the study or been lost to follow-up and corresponding outcome data have been entered onto the trial database and validated as being ready for analysis. All other outcome measure analyses will be undertaken when the final participant (as defined above) reaches their 36-month assessment.

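### The one check on unfinished heights that the article names drops children by a post-randomisation status, so its agreement with the primary result is weak evidence of robustness

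*Protocol article*

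**What the plan says.** All places are in the protocol article; the SAP is not at hand.

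- **Unfinished heights.** Under Missing data and sensitivity analyses, a child with a height who is not at near FH stays in the primary analysis with the end-of-study height. The article expects this to be rare but gives no rate. It then says "we will conduct a sensitivity analysis (for the primary outcome only) which excludes any participants who have not reached near FH", and refers to the SAP for full details. Multiple imputation and last observation carried forward are named in the same section, but for missing primary outcome data. An unfinished height is not missing, because a value is substituted.
- **Near FH.** Planned final analyses requires a growth rate below 2 cm/year and that children "have reached a bone age of 14 years (females) or 16 years (males"). The Fig. 2 legend assigns the two bone ages to the opposite sexes. Study procedures uses growth rate alone.
- **Follow-up.** Planned interventions follows both arms "until near FH or the 36-month follow-up (whichever is soonest"). The Fig. 2 legend allows longer follow-up for children not at near FH by 3 years.
- **Bone age as an outcome.** Secondary outcomes lists bone age delay and bone age acceleration, and the section on their analysis compares them between arms.
- **Decision rule.** Under Primary outcome measure, non-inferiority rests on the ITT and per-protocol analyses, with the lower 95% limit above −0.55 in both.

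**The concern.** Whether a child counts as finished is settled after randomisation, from growth rate and bone age. The trial compares continuing with stopping GH and treats bone age change as something that may differ by arm. Restricting to finished children therefore selects on a possible consequence of treatment. If the arms mature at different speeds, and speed is related to final height, the children left in the two arms are no longer comparable.

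What is at stake is how the check will be read. It exists to show whether substituting unfinished heights drives the result. If it agrees with the primary analysis, readers will take that as support. Yet it swaps a truncation bias for a possible selection bias. These two biases can share a sign, and the result itself does not reveal whether they do.

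**Working it through.** **1. The plan's own figures.** Inputs from Sample size and power calculation: "a non-inferiority margin of 0.55 near FH-SDS, a one-sided test with alpha = 0.025 and 90% power, a group size of 57"; "This calculation was based on a near FH-SDS (SD) of − 1.6 (0.9"); "With 17% allowance for withdrawal and loss to follow-up, a total sample size of 138 is required". Allocation is "randomised at the level of the individual in a 1:1 ratio".

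- n per arm = 2 × (1.960 + 1.282)² × 0.9² / 0.55² = 56.3, so 57 per arm and 114 in total.
- 114 / (1 − 0.17) = 137.3, so 138.

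Both figures reproduce, and power at 57 per arm is 90.4%. Nothing below changes the sample size.

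**2. Bias of the completers-only comparison.** Assumptions, none from the documents: final height is normal with SD 0.9; it correlates ρ with a latent lateness score; a share u with the highest scores is unfinished. With c the (1 − u) normal quantile and φ the normal density, excluding unfinished children moves an arm's mean by

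shift(u) = −ρ × 0.9 × φ(c) / (1 − u).

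For ρ = 0.4:

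| u | φ(c) | shift (SDS) |
|---|---|---|
| 2% | 0.048 | −0.018 |
| 5% | 0.103 | −0.039 |
| 10% | 0.175 | −0.070 |
| 20% | 0.280 | −0.126 |
| 30% | 0.348 | −0.179 |

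Bias of the difference (GH− minus GH+) = shift(u in GH−) − shift(u in GH+):

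- Equal shares: 0. ρ = 0: 0 for any shares.
- GH+ 10%, GH− 2%: −0.018 + 0.070 = +0.052.
- GH+ 20%, GH− 5%: −0.039 + 0.126 = +0.087, or 16% of the margin (0.087 / 0.55).
- GH+ 30%, GH− 10%: −0.070 + 0.179 = +0.109, or 20% of the margin.
- Reversing the sign of ρ, or swapping the arms, reverses the sign of the bias.

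**3. What this does to the conclusion.** Simulation: 57 per arm, SD 0.9, true difference exactly −0.55, 20,000 runs per setting, unadjusted comparison. Remaining growth of unfinished children is assumed to be 0.3 or 0.6 SDS. The article says the margin "approximates to 3.8 cm for boys and 3.3 cm for girls at age 23", so these are about 2.1 and 4.1 cm for boys (0.3 and 0.6 × 3.8 / 0.55) and 1.8 and 3.6 cm for girls. The table gives the rate of wrongly concluding non-inferiority (nominal 2.5%); ranges span the two remaining-growth values and, in the first row, the settings pooled there.

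| Unfinished GH+ / GH− | ρ | Primary | Completers only | Both wrong |
|---|---|---|---|---|
| equal, 2% or 10% | any | 2.3–2.9% | 2.3–2.8% | 1.3–2.5% |
| 20% / 5% | +0.4 | 4.4–7.9% | 6.9–7.1% | 3.7–5.5% |
| 20% / 5% | 0 | 4.5–7.6% | 2.5–2.6% | 2.2–2.4% |
| 20% / 5% | −0.4 | 4.4–7.0% | 0.7–0.8% | 0.6–0.7% |
| 5% / 20% | −0.4 | 0.7–1.3% | 6.9–7.0% | 0.7–1.2% |

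With more unfinished children in GH+, the check supports a wrong primary result if those children end up taller, is valid if being unfinished is unrelated to final height, and contradicts the wrong result if they end up shorter. With more in GH−, the primary analysis is conservative and joint error is below nominal.

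**4. Sensitivity to how rare non-attainment is.** A second assumed model takes time to near FH as normal with SD 0.75 years, a 3-year cut-off, ρ = 0.4 and one arm later by 0.5 years. The earlier arm's unfinished share is given first. The first bias delays one arm by the full 0.5 years; the bias in brackets splits the delay evenly around the mean.

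- Mean 3.0 years (50%): 0.17 (0.15) SDS.
- Mean 2.0 years (9%): 0.09 (0.07) SDS.
- Mean 1.5 years (2%): 0.045 (0.03) SDS.

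**The case against.** The case on the other side is substantial.

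- The article leaves full details to the SAP, so the exclusion may not be the only check planned. This stands: the point is limited to the checks the article names.
- The exclusion analysis does not enter the decision rule, and the primary analysis keeps the randomised groups. This stands. A reader might infer that the trial's randomisation is broken; only this one comparison loses its protection.
- The article expects non-attainment to be rare, and presents 3 years as an allowance covering the usual time to near FH. A reader might take the Discussion's remark about stopping GH approximately 3 years earlier to mean that about half the children will be unfinished. With half excluded, the interval half-width would be 1.96 × 0.9 × √(2/28.5) = 0.47 SDS instead of 0.33, and power about 64%. But that remark concerns treatment time saved and gives no distribution of time to near FH, so the documents do not support that share. The 0.17 SDS figure rests on it too.
- No passage says which arm will have more unfinished children or how they differ in final height. Listing bone age acceleration as an outcome does not establish that GH changes it. A reader might infer that the check will tend to confirm a wrong result; that follows only under one combination of signs.
- The planned model adjusts for baseline height SDS, sex, Tanner stage and centre, and the calculations above do not. Adjustment may reduce the bias.

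What survives is that the analyst cannot tell from the completers-only result which of these settings applies. Agreement with the primary analysis is therefore not reliable evidence of robustness.

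**Conclusion.** The point holds in limited form. The one check on unfinished heights named in the article conditions on a post-randomisation status that treatment may affect, and it should not serve as the main evidence that those heights do not matter. The bias is nil with equal shares (and the same link to final height in both arms) or with no correlation, and small if non-attainment is as rare as the article expects. It is about 0.05 to 0.11 SDS, in either direction, for the unequal shares examined with ρ = ±0.4. Shares and correlations are assumptions, because the documents give neither.

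The larger weakness is the substitution that the check is meant to test. With 20% of GH+ and 5% of GH− unfinished, a true difference of −0.55 appears as −0.55 + 0.15 × 0.3 = −0.505, or −0.55 + 0.15 × 0.6 = −0.46. This is a reason to have a better check, not a reason to think that the trial's conclusion will be wrong.

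**What to change.** In Missing data and sensitivity analyses, and in the SAP:

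1. Make the main sensitivity analysis for unfinished heights one that keeps every randomised child with a height. Impute or add remaining growth for those not at near FH (for example from height, growth rate and bone age) over a prespecified range varied separately by arm.
2. Report the arm difference in remaining growth at which the non-inferiority conclusion changes.
3. Report the share not at near FH by arm.
4. Keep the completers-only result as descriptive.
5. Reconcile the near-FH definitions in the Fig. 2 legend, Study procedures and Planned final analyses, and the follow-up limits in Planned interventions and the Fig. 2 legend. They decide who counts as unfinished.

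The cost is wording and a few more model runs, with no change in sample size. Heights are already measured every 6 months. The text schedules hand X-rays at enrolment and near FH, so confirm in the full schedule that a bone age exists at the last visit for unfinished children; if not, set the range from height and growth rate. The article reports no recruitment at publication, so the change could be prespecified before outcome data accrue.
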